#### Phase II

This trial will include a different group of 20 patients from the same hospital who meet the inclusion criteria described above, who will also sign the corresponding consent forms prior to initiation of collaboration. After having set the maximum tolerated training time per session in the phase I trial, a 15-day phase-II trial will be designed to ascertain the effectiveness of the CCT in the absence of adverse events or side effects.

To this end, 20 patients from the Sleep Unit of the Hospital Universitario de la Ribera (Spain) will be recruited and they will first complete an initial session (Day 1) that will serve to collect baseline data about their sleep problems and their cognitive skills, as well as about their sociodemographic information. As in the phase I trial, they will complete the general cognitive and psychological evaluation lasting for around 60 min (see Instruments and Outcome Measures section).

The day after the initial evaluation (Day 2), participants will be asked to visit the Sleep Unit again to complete the first training session with the CCT. The duration of the training session will be determined by the results of the phase I trial. Participants will complete this training session using either a tablet, a PC or a laptop, accompanied by the research and clinical team. Right at the end of the session, and in order to assess the safety of the intervention, participants will also complete the same safety questionnaire as in the phase I trial. In case any participant at any moment would report potential adverse events in any of the safety questions, the clinical psychologist would immediately interview them in order to classify the side effect or adverse event according to its seriousness following the criteria and elements adapted from the Patient-Reported Adverse Drug Event Questionnaire (de Vries et al., 2013).

The protocol would then continue the next day (Day 3) with a full assessment identical to that of the first session. The day after (Day 4) would consist of the repetition of the training session of Day 2. This way, and alternating assessment and training sessions, participants will complete a 15-day cycle that will start and end with a full assessment (Day 1 and Day 15), and that will include eight different evaluation or test points (Day 1, Day 3, Day 5, Day 7, Day 9, Day 11, Day 13, and Day 15) and seven training sessions (Day 2, Day 4, Day 6, Day 8, Day 10, Day 12, and Day 14).

The results of the effectiveness of the CCT will be evaluated using linear mixed models for repeated measures, analyzing differences in the primary and secondary outcomes described below. This will provide a first approach to and statistical validation of the usefulness of the CCT to alleviate the cognitive, psychological or medical symptoms of insomnia in the selected sample by determining the minimum number of training sessions needed to observe a significant change. Besides, quantitative and qualitative analysis of the results of the safety questionnaires will help us determine the safety of the intervention program.

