### Participant Selection and Sample Sizes

Participants will be recruited from the Sleep Unit of the Hospital Universitario de la Ribera (Spain) for the phase-I and phase-II trials, and from the same Unit and associated medical centers for the phase-III trial. According to the *a priori* established eligibility criteria, participants will be adults between 25 and 55 years old who have been diagnosed by Insomnia Disorder according to DSM-5, fully matching the diagnostic criteria (e.g., showing a predominant complaint of dissatisfaction with sleep quantity or quality occurring at least three nights per week and having been present for a minimum of 3 months, despite them having adequate opportunity for sleep and in the absence of sleep-wake disorders or the use of substances, which causes clinically relevant impairment). We selected this age range in an attempt to improve sample homogeneity in executive function development (see Ferguson et al., 2021), and to ensure that participants would have access to new technologies. Participants will be excluded from the study if they meet any of the following *a priori* established criteria: (1) they present another sleep-wake disorder (e.g., narcolepsy, restless leg syndrome, a breathing-related sleep disorder, a circadian sleep-wake rhythm disorder, a parasomnia); (2) they present a relevant medical, psychiatric or neurological disorder; (3) they show significant visual or motor impairments; (4) they present history of alcohol or drug abuse or dependence; (5) they show a caffeine consumption higher than 150 mg per day or an alcohol consumption higher that 250 ml per day; (6) they use medication with stimulant action, except the sedatives or hypnotics specifically prescribed for sleep.

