The phase-I trial will follow a standard 3 + 3 protocol. Consequently, the minimum number of participants will be three, and the maximum number of participants will depend on the results of each of the 3-patient cohorts. The phase-II trial will include 20 insomnia patients. Finally, the phase-III trial will consist of a minimum sample size set at 60 participants per group, given that the purpose of this research is to make a first approach to the positive impact of a cognitive training of executive functions on insomnia and to be able to generalize the results obtained with a 95% confidence interval and sufficient statistical power to test hypotheses (sig. bilateral). While a larger number of participants would be desirable for a phase-III trial, it should be considered that the specific selection criteria of the sample and the restricted number of patients that are available at the hospital and the associated centers make it difficult to increase the sample size to account for potential attrition rates and lack of adherence.

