##### Worrying

The Penn State Worry Questionnaire (PSWQ) will be used. The PSWQ is a 16-item questionnaire that aims to measure the trait of worry. The items on the scale assess the occurrence, intrusiveness, pervasiveness, and other characterizing features of an individual’s experience with worry. The scale has been shown to identify worry, over and above anxiety and depression. Items are rated on a five-point scale: 1-Not at all typical of me to 5-Very typical of me. Possible scores range from 16 (low worry) to 80 (high worry).

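### Phase II reads a minimum number of sessions from questionnaires repeated every two days, so for instruments that look back a week or more that number is confounded with the reference period

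*Protocol article*

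**What the plan says.** The Phase II section sets a 15-day cycle in which assessment and training alternate. Assessments fall on the odd-numbered days, eight in all, and training falls on the even-numbered days, seven in all. The first repeat comes one night after the first session and uses the same content as baseline: "The protocol would then continue the next day (Day 3) with a full assessment identical to that of the first session".

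The analysis uses "linear mixed models for repeated measures, analyzing differences in the primary and secondary outcomes described below", and its product is the session count: "determining the minimum number of training sessions needed to observe a significant change". The sample is a single group: "The phase-II trial will include 20 insomnia patients".

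The outcomes, as described under Instruments and Outcome Measures, differ in what period they refer to:

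- Worry: "The PSWQ is a 16-item questionnaire that aims to measure the trait of worry".
- PROMIS: four of the five listed questions ask about the respondent's state in general.
- PSQI, ISI, WHOQOL-BREF, BRIEF-A and BDI-II: no reference period is given.
- STAI: only the state items are used.
- CAB: a performance test. After the first administration its scores are updated from performance on the training tasks.

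**The concern.** A session count can be read from repeated scores only if each score describes the interval since the previous one. Here that interval is two days. An instrument that looks back a week or longer, given in the same form each time, covers many of the same nights at successive visits. At the early visits, most of those nights fall before any training. Its score would then move gradually even if the training worked from the first night, and the visit at which the change becomes significant would depend partly on how far back the form asks. A trait scale, or one that asks about health in general, has no short window at all.

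The number of sessions needed is part of the second study objective. For the primary sleep and quality-of-life outcomes, the schedule as written cannot separate that number from the length of the reference period. Patients would also repeat a battery of about 60 minutes eight times, and the interim scores on these scales could not be interpreted session by session.

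**Working it through.** **Schedule.** The odd days from 1 to 15 give 8 assessments and the even days from 2 to 14 give 7 sessions. Both match the protocol.

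**Share of the window after training began.** Session 1 is on Day 2, so at assessment day d there have been d − 2 nights since training began: 1 on Day 3, 3 on Day 5, and so on to 13 on Day 15. For a reference period of W nights the post-training share is min(1, (d − 2)/W). The protocol does not state W, so 7, 14 and 30 nights are assumed.

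| Day (sessions done) | W = 7 | W = 14 | W = 30 |
|---|---|---|---|
| 3 (1) | 14% | 7% | 3% |
| 5 (2) | 43% | 21% | 10% |
| 7 (3) | 71% | 36% | 17% |
| 9 (4) | 100% | 50% | 23% |
| 11 (5) | 100% | 64% | 30% |
| 13 (6) | 100% | 79% | 37% |
| 15 (7) | 100% | 93% | 43% |

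On Days 3 and 5 the share is below one half for all three windows. It stays below one half at every visit only if 13/W < 0.5, that is, if W exceeds 26 nights.

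**Effect on the session count.** This is an illustration, because the protocol gives no effect size, significance level or power for Phase II. It uses a paired t test against Day 1 with n = 20 (from the protocol) and a two-sided 5% level (assumed). The true standardised change D is taken as fully present from the night after session 1 (assumed), and the score is taken to average evenly over the window (assumed). The observed standardised change is then D × share. Power comes from the noncentral t with 19 degrees of freedom and noncentrality D × share × √20. For example, with D = 1.0 and W = 7 on Day 5, the noncentrality is 0.429 × 4.472 = 1.92 and the power is 44%.

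Power at D = 1.0 (99% if the effect is seen in full):

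| Sessions done | W = 7 | W = 14 | W = 30 |
|---|---|---|---|
| 1 | 9% | 6% | 5% |
| 2 | 44% | 15% | 7% |
| 3 | 86% | 33% | 11% |
| 4 | 99% | 56% | 17% |
| 5 | 99% | 78% | 25% |
| 6 | 99% | 91% | 34% |
| 7 | 99% | 98% | 45% |

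First session count with at least 80% power:

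| D | W = 1 | W = 7 | W = 14 | W = 30 |
|---|---|---|---|---|
| 0.8 | 1 | 4 | 7 | not by 7 (31%) |
| 1.0 | 1 | 3 | 6 | not by 7 (45%) |
| 1.5 | 1 | 3 | 4 | not by 7 (79%) |

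Across a row the true effect is the same and the derived count changes with W. Down the W = 14 column the count falls as the effect grows, so the effect still contributes to it.

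**The case against.** The strongest reply is that the reference periods are not in the document, so the size of the problem is assumed. That stands, and it is why a range is shown. The eligibility text ("occurring at least three nights per week and having been present for a minimum of 3 months") does not fill the gap, because it is a diagnostic criterion and not the window of any scale. The illustration also assumes an immediate effect and even averaging over nights, neither of which the protocol states. If the effect builds up over sessions, one session is not the true answer.

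Three stronger readings are tempting and not supported:

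- A reader might infer that every score at every visit mostly describes nights before training. That needs a window above 26 nights. With 7 nights it fails from Day 7, and with 14 nights the share reaches one half on Day 9.
- A reader might infer that the count reflects the window and not the effect. It reflects both, as the W = 14 column shows.
- A reader might infer a bias toward too many sessions. Dilution pushes that way, but Phase II describes no control group and gives the battery eight times. Repeated testing or the passage of time could produce early significance, so the net direction is not established.

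Two limits of scope also stand. The state-anxiety items and the CAB do not refer to past nights. And Phase III is fixed at 8 weeks of five sessions, 40 in all, with session length taken from Phase I, so the Phase II count sets nothing there.

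The central point remains. The protocol itself calls the repeat assessment identical, calls one scale a trait measure and words most PROMIS items generally, yet draws the session count from all outcomes alike.

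**Conclusion.** The point holds for the retrospective, trait and general-state questionnaires in Phase II. For any of them with a reference period of a week or more, the Day 3 and Day 5 scores mostly cover nights before training (post-training share 3–14% and 10–43% over an assumed 7 to 30 nights). The session number at first significance is therefore confounded with that period. In the illustration with a change of 1.0, the same true effect gives 3 sessions, 6 sessions or none within 7, depending only on the window. The shares follow from the protocol's schedule once a window is assumed. The power figures also rest on the assumed effect, its immediate onset and even averaging. The damage is confined to the Phase II objective on the number of sessions.

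**What to change.** In the Phase II section:

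- Analyse the retrospective, trait and general-state questionnaires (PSQI, ISI, WHOQOL-BREF, PROMIS, BRIEF-A, BDI-II, PSWQ) as a single Day 1 to Day 15 change, and draw no session number from them. State the reference period of each: with a 30-night window even the Day 15 score is only 43% post-training.
- Limit the minimum-sessions inference to measures whose reference period does not exceed the two-day spacing, such as state anxiety. Include the CAB only if it is administered again at each assessment and not recalculated from training performance.
- If an interim sleep signal is wanted, add sleep items that refer only to the time since the last assessment and label them exploratory, since they would not be the standard forms.

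The cost is a change of wording, and patients can be spared the interim questionnaires. The downside is that the session-number claim is given up for the standard sleep and quality-of-life indices.

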## Abstract

Insomnia is a frequent and heightened pathology in the general population of developed countries, and its condition generally leads to health discomfort and performance drop in daily and work-related tasks. As current pharmacological treatments for insomnia do not always seem sufficient to mitigate impairment, contemporary cognitive approaches might shed light on developing complementary therapies for this population. We propose a cognitive stimulation intervention program based on the importance of cognitive abilities as precipitating and maintenance variables of sleep disturbances. A full phase I-II-III clinical trial is proposed in which the first two studies will serve to assess the safety of the intervention and to identify the maximum tolerated time of the computerized cognitive training (phase I) and the minimum effective number of training sessions (phase II) in the absence of adverse events or side effects. Next, a phase-III double-blind randomized controlled trial design will be set. Sixty individuals with insomnia aged 25 to 55 years will enroll in a home-based personalized computerized cognitive stimulation program for a total time of 8 weeks, training 5 days per week. Sixty insomnia patients matched in a variety of factors will constitute the active control group, where the orthogonal activities will not be cognitively demanding. Sleep, cognitive, emotional, and quality of life variables will be measured before and immediately after training. A linear mixed model and hierarchical regression analysis will be used to investigate intervention effects. The results derived from this study will be precious for future research and treatment in cognitive performance and clinical pathologies.

**Clinical Trial Registration:** [https://clinicaltrials.gov/], identifier [NCT05050292].

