## The Current Proposal

Given the disadvantages of pharmacological treatment for insomnia in the long term and the high costs of CBT-I, and considering the usefulness of computerized cognitive training (CCT) as an aid, the development of new lines of intervention in this perspective is deemed crucial. Based on the existing literature on the precipitating and maintenance factors of insomnia, we propose a research agenda with the proposal of a clinical trial aimed at demonstrating the safety and efficacy of an intervention based on a personalized CCT focused on the improvement of the cognitive components related to the processes of inhibition, attention, perception, and processing of stimuli, in order to partially compensate the problems related with cognitive states of concern and alert typically present in patients with insomnia disorder. To this end, a full phase I-II-III study protocol is presented. While the core of the intervention will be the phase-III randomized controlled trial, a safety and dose-limiting analysis protocol has also been designed as part of the phase-I/II trials to provide informed decisions. A phase-I trial will be conducted in order to assess the safety of the CCT and to determine the maximum tolerated training time per session (equivalent to the maximum tolerated dose of a medicine). Next, a phase-II trial will also be run to validate the safety of the CCT while determining the minimum necessary training sessions to observe significant effects (namely, to test the efficacy of the CCT). Finally, the critical phase-III trial will be carried out through an online platform of personalized CCT programs (CogniFit Inc., San Francisco, CA, United States), which will be administered to a group of patients with insomnia, while a different group of participants of similar characteristics will complete a control intervention lacking high cognitive demands and based on the completion of low-level computerized artistic tasks.

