## Objectives and Hypotheses

Given the findings that show that the excessive cognitive activity present in patients with insomnia is due to a deficit in the functioning of various cognitive functions related to attention and executive functions, we hypothesize that a systematized training in such functions will act as a catalyst on cortical hyperactivity, limiting rumination, intrusive thoughts and disturbing stimuli, thus improving the quality of sleep. We postulate that insomnia patients will also benefit from a general cognitive performance enhancement when CCT mainly targets cognitive functions.

Therefore, the present study has three main objectives: (1) establish the acceptable sessions’ range to determine the maximum training time before fatigue or other adverse conditions appear; (2) determine the therapeutic efficacy of the intervention, establishing the range of needed training sessions, the tolerability to exercises, and the safety of the activity; and (3) verify that CCT can be a plausible non-pharmacological intervention to improve sleep quality in insomnia individuals.

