Next, the CCT intervention will be carried out. This will be done through the CogniFit online platform so that each participant will access it from home using a personal computer or smart device. The training will last for a total of 8 weeks, with five training days per week. This way, a total of 40 training sessions are expected. The duration of the sessions will be determined by the maximum tolerated training time resulting from the phase-I trial. Since this process will be autonomously managed by each participant, they will be contacted periodically (a minimum of two phone calls per week) to ensure adherence and check that they have not had any incidence. The platform will record participants’ performance, providing researchers with real-time feedback on the performance and adherence of each participant.

Participants will be randomly assigned to one out of two groups (control/experimental). The experimental group will complete a personalized CCT intervention based on CogniFit’s Personalized Online Training, including a series of games and activities targeting attention, memory and executive functions. The difficulty level of each of the activities will dynamically change to match the cognitive profile of each participant on each training day. By automatically adjusting the activities’ difficulty and requirements according to each participant’s performance, cognitive taxing is adapted and a maximum cognitive effort is always required. Similar to Haimov and Shatil (2013), the active control group will complete a series of painting activities specifically designed not to result cognitively demanding and to maintain a low complexity level and constant difficulty throughout the intervention. These activities will not target the intended cognitive processes (namely, they will target orthogonal unrelated aspects). Participants will be randomly assigned to either the experimental or control group, with the experimenters and the patients being fully blind to the group classification.

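### Phase II takes a minimum effective number of sessions from first significance in one uncontrolled group, where session count cannot be separated from retesting or time

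*Protocol article*

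**What the plan says.** The Phase II section describes one group of 20 patients, all trained, with no comparator. Everyone follows the same 15-day cycle: eight assessments on odd days, each "with a full assessment identical to that of the first session", and seven training sessions on the even days between. Linear mixed models for repeated measures are applied to the primary and secondary outcomes, and the result is obtained by "determining the minimum number of training sessions needed to observe a significant change".

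The meaning given to that number varies across the protocol article:

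- **Abstract:** Phase II identifies "the minimum effective number of training sessions (phase II) in the absence of adverse events or side effects".
- **The Current Proposal:** Phase II is for "determining the minimum necessary training sessions to observe significant effects (namely, to test the efficacy of the CCT").
- **Objectives and Hypotheses, Objective 2:** "determine the therapeutic efficacy of the intervention, establishing the range of needed training sessions".
- **Phase II, opening:** "a 15-day phase-II trial will be designed to ascertain the effectiveness of the CCT".
- **Phase II, analysis:** "This will provide a first approach to and statistical validation of the usefulness of the CCT". This is softer in its first half and not in its second.

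Phase III does not use the Phase II number. Its schedule is set in advance, and "a total of 40 training sessions are expected".

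**The concern.** Two things are wrong with the rule.

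First, it attributes change since Day 1 to the number of training sessions. By the time a patient has had k sessions, that patient has also taken the full battery k times before, and 2k days of attention, contact and natural fluctuation have passed. Retest practice, regression to the mean and non-specific response would all appear as an effect of sessions. The Expected Results section accepts that taking part without the training could bring some improvement. It says this of the Phase III control group, and expects such change to be minor, and either non-significant or in unrelated functions. Phase II has no group that could show how large that part is.

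Second, the first visit at which a change is significant is not a property of the training. It depends on how many patients were enrolled.

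At stake is Objective 2, one of the study's three main objectives. Followed as written, Phase II would report a minimum effective number of sessions and an efficacy conclusion that its design cannot deliver.

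**Working it through.** The protocol article gives no effect size, SD, alpha or power for Phase II, so there is no stated figure to reproduce.

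**1. Can session count be separated from retesting and time?** Inputs are the assessment and training days in the Phase II section. No assumptions are needed.

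| Assessment day | 1 | 3 | 5 | 7 | 9 | 11 | 13 | 15 |
|---|---|---|---|---|---|---|---|---|
| Sessions completed | 0 | 1 | 2 | 3 | 4 | 5 | 6 | 7 |
| Earlier assessments | 0 | 1 | 2 | 3 | 4 | 5 | 6 | 7 |
| (Day - 1)/2 | 0 | 1 | 2 | 3 | 4 | 5 | 6 | 7 |

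The columns (1, k, k, 1+2k) for k = 0 to 7 have rank 2, and the three time-varying columns have pairwise correlations of exactly 1. Change over time can be estimated. Its division between sessions, retesting and elapsed time cannot.

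**2. Does first significance depend on n?** Assume a two-sided test of each visit against Day 1. Alpha is 0.05 (the article mentions two-sided testing and a 95% interval only for Phase III) or 0.05/7 for the seven post-baseline visits. The just-significant mean change, in SDs of the within-patient change, is

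t(1 - alpha/2, df) / sqrt(n), with df = n - 1 (paired test) or 7(n - 1) (pooled error).

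| alpha, error term | n=20 | n=40 | n=60 |
|---|---|---|---|
| 0.05, paired | 0.468 | 0.320 | 0.258 |
| 0.05, pooled | 0.442 | 0.311 | 0.254 |
| 0.05/7, paired | 0.674 | 0.449 | 0.360 |
| 0.05/7, pooled | 0.611 | 0.429 | 0.349 |

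Relative to n=20, the threshold falls to 0.67-0.70 at n=40 and 0.53-0.57 at n=60, whichever alpha is chosen.

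Now assume also that change grows in proportion to sessions, and take a curve that just reaches significance at session 7 with n=20. With n=40 it does so at 7 x 0.666 to 7 x 0.704, that is 4.66 to 4.93, so at session 5. With n=60 the products run from 3.74 to 4.02, so session 4 or 5. The training is the same and the minimum number differs.

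**3. How often would the rule return a number with no training effect?** This is a simulation and rests on assumed inputs: n=20, outcome SD 1, equal correlation between visits, and unadjusted paired tests at two-sided 0.05 standing in for the mixed-model visit contrasts. The training effect is zero throughout.

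| Non-specific drift per two-day step | Correlation | Trials declaring some minimum number, per outcome |
|---|---|---|
| None | 0.5-0.8 | about 23-24% |
| 0.05 SD | 0.7 | about 70% |
| 0.05 SD | 0.5-0.8 | about 55-82% |
| 0.10 SD | 0.7 | about 99% |
| 0.10 SD | 0.5-0.8 | 94% or more |

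Over the seven steps these drifts total 7 x 0.05 = 0.35 SD and 7 x 0.10 = 0.70 SD. At 0.10 SD per step and correlation 0.7, the median first significant session is 5 with n=10, 4 with n=20, 3 with n=40 and 2 with n=60. The no-drift row reflects unadjusted testing, which an analysis plan could correct. The drift rows come from the missing comparator, and no adjustment of alpha can attribute that drift correctly.

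**The case against.** The strongest reply is that little depends on this. No stated feature of Phase III uses the Phase II number: the 40 sessions are preset, session length comes from Phase I, and efficacy is tested against a randomised active control. The Current Proposal calls Phase III the core and presents Phases I and II as safety and dose-limiting work to inform decisions, and the Phase II analysis text speaks of a first approach in the selected sample. Collinearity of dose and time is also the ordinary limit of any single-arm, fixed-schedule study, and looking for a preliminary signal in such a study is legitimate.

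Much of this stands, and it limits the severity. The point remains, because the protocol does not stop at a preliminary signal. It defines a minimum number of sessions by significance, equates that with testing efficacy and makes it a main objective. The preparatory framing does not withdraw those statements. An analysis plan cannot repair the claim either, since the confounding comes from the schedule and the missing comparator. Missed or shifted visits would break the exact collinearity, but not at random, so they would not rescue the inference.

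On the numbers, it is fair that n=40 and n=60 are not proposed, that the linear curve is assumed, and that the choice between session 4 and 5 at n=60 is largely rounding (3.999 against 4.02). Those figures serve only to show that the rule's answer moves with enrolment. The drift sizes in the simulation are assumptions too. The Expected Results text is weak evidence of drift over 15 days, and the argument does not depend on it.

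**Conclusion.** The concern holds. The non-identifiability follows from the schedule alone (four columns, rank 2) and needs no assumption. The dependence on sample size needs only that each visit is tested two-sided against baseline: the threshold at n=40 is about two thirds of that at n=20, at either alpha. The rates at which a number is declared without any training effect (roughly 55-82% and 94% or more) depend on assumed drifts of 0.05 and 0.10 SD per step and are illustrations.

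The consequence is an unsupported conclusion for the efficacy and session-range parts of Objective 2. Phase II's safety and tolerability aims and the Phase III comparison are not affected. The protocol should be changed on this point, but the point does not threaten the main trial.

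**What to change.** In the Abstract, The Current Proposal, Objective 2 and the Phase II section:

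- Remove the rule that reads a minimum number of sessions from significance, and remove the efficacy and effectiveness wording for Phase II.
- Describe Phase II as a study of safety, tolerability and feasibility.
- Keep the repeated-measures model, but report change over the seven sessions as an estimate with a 95% confidence interval, labelled as uncontrolled and not attributable to training dose.
- Leave efficacy to the randomised Phase III. Its 40-session schedule need not change.

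A secondary caution concerns the Cognitive Assessment Battery. The Cognitive Skills section says its scores are recalculated from performance in the training tasks after the first administration, while the Phase II section says each assessment is identical to the first. If the Phase II scores are the recalculated ones, they should not be used as evidence of a session-number effect.

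The change adds no patients, visits or procedures. The sponsor gives up the claim to a minimum effective number of sessions and the efficacy and session-range parts of Objective 2 for Phase II. Keeping that aim would need a concurrent control or randomised session numbers. That is a larger redesign and is not asked for here.
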